#### Cost‐effectiveness analysis

2.7.3

A joint comparison of costs and MACE will be performed by nonparametric bootstrapping with 1000 re‐samples. A distribution will be attributed to each variable according to accepted practice: normal distribution for MACE and log normal or Beta for costs. The results of the bootstrap replications will be presented on a cost‐effectiveness plane. In addition to the cost‐effectiveness plane, acceptability curves for French and Spanish values will be plotted.

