### Study outcomes

2.3

The primary outcome is the incremental cost‐effectiveness ratio (ICER) at 30 days, using major adverse cardiovascular events (MACE) (composite of all‐cause death, nonfatal stroke, nonfatal recurrent myocardial infarction, or emergency revascularization prompted by ischemia) as the effectiveness criterion. The primary and various secondary outcomes are listed in Table 2.

**TABLE 2 clc23453-tbl-0002:** Outcomes of the REALITY trial

Outcomes	Details
Primary clinical effectiveness composite outcome	
Clinical noninferiority at 30 d	MACE^a^ at 30 days
Primary endpoint	
ICER at 30 d	ICER at 30 days, using the 30 day composite endpoint of MACE^a^ as the effectiveness criterion
Secondary endpoints	
Exploratory outcomes at 30 d	All the components^a^ of the composite clinical outcome will be analyzed separately
Component ICERs at 30 d	ICERs for each individual component of the primary endpoint will be estimated separately
Clinical noninferiority at 1 y	MACE^a^ at 1 y All the components^a^ of this composite clinical outcome will also be analyzed separately as secondary endpoints
ICER at 1 y	ICER at 1 year, using the 1 y composite endpoint of MACE^a^ as the effectiveness criterion
ICUR at 1 y	ICUR at 1 year using QALY at 1 y

Abbreviations: ICER, incremental cost‐effectiveness ratio; ICUR, incremental cost‐utility ratio; MACE, major adverse cardiovascular events.

^a^ All‐cause death, nonfatal stroke, nonfatal recurrent myocardial infarction, or emergency revascularization prompted by ischemia. All components of the composite outcome will also be analyzed separately.

All clinical outcomes (deaths, including cause of death, AMIs, strokes, ischemia‐driven emergency revascularizations, and heart failures) will be reviewed and adjudicated by a CEC. The CEC will be given all relevant clinical and biochemical information and will be blinded to the randomization assignment. In addition, AMIs will be categorized by the CEC according to the Third Universal Definition.^18^ Each triggered event will be reviewed by two CEC members. In case of discrepancy between the two adjudicators, an ad hoc committee with at least three CEC members will reach a final decision based on consensus.

Safety outcomes of special interest, which will be monitored during the index hospitalization, include hemolysis, infections, multiorgan system dysfunction, acute lung injury, acute heart failure, acute renal failure, and severe allergic reactions.

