### Health‐economic analysis

2.4

A cost‐effectiveness primary outcome (30 day ICER) was chosen due to its frequent use in cardiology and the availability of benchmarks for the cost‐effectiveness results.^19^, ^20^ The BASKET trial has provided a benchmark for the acceptable cost per MACE averted with an ICER of 64 732 euros to prevent one major adverse cardiac event.^21^ The secondary health outcome for the cost‐utility analyses is quality‐adjusted life years (QALYs) at 1 year. These are calculated for both groups using health‐related quality of life (HRQoL) scores from the EuroQoL five dimensions (EQ‐5D) questionnaire and converted to utility scores using country weights.^22^, ^23^

The cost‐effectiveness analysis of the costs and outcomes for patients in the restrictive and liberal transfusion groups will be conducted from the perspectives of both the French and Spanish governments (providing a healthcare system perspective for both countries). This perspective allows comparisons with the results of other economic evaluations in cardiology. The economic evaluation will be based on the entire population of patients in the trial. Unit costs are undiscounted and are presented in Tables S1 and S2. Resources will be collected prospectively at the patient level. Prespecified subgroup analyses by country are necessary due to potential differences in unit costs and resource utilization.^24^

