#### Power and sample size considerations

2.7.1

There is no established clinical superiority of either transfusion strategy at this stage. We hypothesized that a restrictive transfusion strategy would be clinically noninferior to a liberal transfusion strategy but less costly. As our hypotheses are clinical noninferiority but superior cost‐effectiveness of the restrictive transfusion strategy, we based our power calculations on clinical grounds. We anticipated MACE rates of 11% in the restrictive transfusion strategy and 15% in the liberal transfusion strategy, based on observations from the nationwide French registry of acute ST‐Elevation or non‐ST‐elevation myocardial infarction (FAST‐MI) program.^25^ Based on these hypotheses, a sample size of 300 patients per group would provide 80% power to demonstrate noninferiority of the restrictive group, with a noninferiority margin corresponding to a relative risk equal to 1.25, using a confidence interval (CI) method with a 97.5% one‐sided CI. With a conservative hypothesis of 5% of patients with major protocol violations, a total of 630 patients (315 in each arm) are required for the trial to be adequately powered for both intention‐to‐treat (ITT) and per‐protocol (PP) analyses. Using the formula for sample size calculation in economic evaluation, we estimated that this sample size would allow us to show cost‐effectiveness at a threshold of €50 000, a power of 80%, and a significance level of 5%, a €1000 difference in costs and 0.15 difference in QALYs.^26^
$$n=\frac{2\;{\left(z_{\propto }+z_{\beta }\right)}^{2}\left({\mathrm{sd}}_{c}^{2}+{\left(\mathrm{Ws}d_{q}\right)}^{2}-\left(2\mathrm{W\rho s}d_{c}sd_{q}\right)\right)}{{\left(W∆Q-∆C\right)}^{2}}.$$where *C* and *Q* represent costs and utilities, *W* willingness to pay, and *ρ* the correlation between costs and quality of life (set at −0.1).

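### The cost-effectiveness section calls the primary bootstrap nonparametric and then assigns distributions to MACE and costs, one of which (Beta) cannot hold euro amounts as written

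*Protocol article*

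**What the plan says.** Section 2.3 (Study outcomes) sets the primary endpoint: "The primary outcome is the incremental cost‐effectiveness ratio (ICER) at 30 days, using major adverse cardiovascular events (MACE", a composite that each patient either has or does not have.

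Section 2.7.3 (Cost-effectiveness analysis) gives the method: "A joint comparison of costs and MACE will be performed by nonparametric bootstrapping with 1000 re‐samples". The next sentence assigns every variable a distribution, described as usual practice: "normal distribution for MACE and log normal or Beta for costs". The replications then feed a cost-effectiveness plane, and acceptability curves are to be drawn for French and Spanish values.

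On the data, section 2.4 (Health-economic analysis) states: "Resources will be collected prospectively at the patient level". It also cites a benchmark from an earlier trial: "an ICER of 64 732 euros to prevent one major adverse cardiac event".

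The article does not say whether the distributions describe patient values or arm means, what they do alongside the resampling, how the choice between log normal and Beta is made, or how costs would be scaled for a Beta.

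**The concern.** A nonparametric bootstrap draws observed patients with replacement and lets the data supply the distribution. Assigning a family to each variable and drawing from it is a parametric simulation. Two analysts following this paragraph could run different analyses of the primary endpoint, each believing it to be the planned one.

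The named families add to the problem. A Beta on 0 to 1 suits a probability, not a cost in euros. A Normal is not a model for a yes/no patient outcome. Naming distributions one variable at a time also says nothing about the link between having an event and costing more. That link affects the spread of points on the plane and the slope of the acceptability curves. This is the only analysis the article describes for the primary endpoint, so its definition should not be open to two readings.

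**Working it through.** Section 2.7.3 carries no figure of its own to reproduce. The check asks what each reading of the paragraph would do.

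**Inputs from the article**
- MACE rates (section 2.7.1): "We anticipated MACE rates of 11% in the restrictive transfusion strategy and 15% in the liberal transfusion strategy".
- 315 patients per arm (section 2.7.1), i.e. 300 × 1.05.
- Value per MACE averted, W = EUR 64,732 (section 2.4, the cited benchmark, used here only as an illustrative threshold).

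**Assumed inputs, not in the article**
- Patient-level cost SD of EUR 5,000 to 15,000.
- Within-arm cost-MACE correlation ρ of 0 to 0.4.

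**Step 1. Normal for MACE, patient level.** SD = √(p(1−p)).
- Restrictive: √(0.11 × 0.89) = 0.3129; share of draws below zero = Φ(−0.11/0.3129) = 36%.
- Liberal: √(0.15 × 0.85) = 0.3571; share below zero = Φ(−0.15/0.3571) = 34%.

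As a model for individual patients this is untenable.

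**Step 2. Normal for MACE, arm level.** SE = SD/√315.
- Restrictive: 0.0176; liberal: 0.0201.
- The chance of a negative arm rate is about 2 × 10⁻¹⁰ or less.
- 95% interval for the risk difference: binomial resampling gives −9.2 to +1.3 percentage points; the Normal gives −9.2 to +1.2. The limits differ by less than 0.1 point before rounding.

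For arm proportions or their difference, which is what the plane plots, the Normal is accurate.

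**Step 3. Families for cost.** Log normal is positive and right-skewed, so it is reasonable. Beta has support 0 to 1; using it for euros needs a stated upper bound to divide by, and none is given.

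**Step 4. Loss of the cost-MACE link, if variables are drawn separately.** With net benefit per patient = −W × MACE − cost,

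Var(incremental net benefit) = Σ over arms of [SD_c² + (W·SD_m)² + 2ρ·W·SD_m·SD_c] / 315.

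Separate draws drop the last term. W·SD_m is 64,732 × 0.3129 ≈ 20,254 (restrictive) and 64,732 × 0.3571 ≈ 23,114 (liberal).

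| Cost SD (EUR) | ρ | SE, link kept | SE, link dropped | Ratio |
|---|---|---|---|---|
| 5,000 | 0 | 1,777 | 1,777 | 1.00 |
| 5,000 | 0.2 | 1,853 | 1,777 | 0.96 |
| 5,000 | 0.4 | 1,926 | 1,777 | 0.92 |
| 15,000 | 0 | 2,104 | 2,104 | 1.00 |
| 15,000 | 0.2 | 2,292 | 2,104 | 0.92 |
| 15,000 | 0.4 | 2,466 | 2,104 | 0.85 |

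For example, at SD 15,000 and ρ = 0.4: link dropped, √[(2 × 15,000² + 20,254² + 23,114²)/315] = 2,104; link kept, add 2 × 0.4 × 15,000 × (20,254 + 23,114)/315 under the root, giving 2,466.

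**Step 5. Simulation cross-check.** Log normal costs with an assumed mean of EUR 10,000 and coefficient of variation 1, 315 per arm, 1,000 resamples per data set. When a MACE multiplies cost by 1, 2 and 3, separate draws of the arm means give an SD of incremental net benefit equal to 1.00, 0.90 and 0.85 times that of the paired bootstrap. The range agrees with step 4.

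**The case against.** The strongest defence is that the operative method comes first and is right. The comparison is called joint, the bootstrap is called nonparametric, and the plane is built from the bootstrap replications. Costs are measured per patient, so resampling pairs is feasible. On that reading the distribution sentence does nothing and the uncertainty is sound. This stands.

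A reader might infer that the paragraph yields invalid uncertainty for the primary endpoint. The article does not support that. It nowhere says the distributions replace the resampling, and it nowhere says costs and MACE are drawn independently; a marginal distribution for each variable does not by itself imply independence. The economic sample-size formula in section 2.7.1 carries a correlation between costs and quality of life (set at −0.1), so dependence between cost and outcome was in view. The 34 to 36% of impossible draws arises only under a patient-level Normal, which is the less natural reading. Nor is Beta the chosen cost model: log normal is offered beside it and is acceptable.

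The consequence is also bounded. The ICER point estimate from the observed differences does not depend on this sentence, and the noninferiority and superiority rules in section 2.7.5 do not use it.

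The defence does not remove the contradiction between adjacent sentences or the misfit of an unscaled Beta to euros. Nor is this a detail left to a fuller plan: it is a rule that is stated, and stated wrongly.

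**Conclusion.** The concern holds as an internal inconsistency in the description of the primary analysis: wrong as written, not shown to invalidate the primary result. The size depends on what is actually run.
- Patient pairs resampled: no error, and the distribution sentence is redundant.
- Distributions replace the resampling and are drawn separately: the SE of net benefit is understated by about 0 to 15% at EUR 64,732 per MACE. This rests on the assumed cost SDs and correlations and on MACE patients costing the same or more.
- Normal used for MACE: negligible effect for arm rates or their difference, harmful only for individual patients.
- Beta used for costs: not workable without a stated rescaling.

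**What to change.** Delete the distribution sentence in section 2.7.3. In its place, state that patients are resampled with replacement within arm, that each patient's cost and MACE status stay together, that both between-arm differences are recomputed in every replicate, and that the plane and acceptability curves are built from those replicate pairs.

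If a parametric version is wanted, label it a sensitivity analysis and give it families that fit (for example Beta for the MACE probability, log normal or Gamma for cost), with a stated correlation between them. Resampling within country and adding a net-benefit confidence interval are optional; the inconsistency does not require them.

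The cost is a few lines of wording, with no programming beyond the bootstrap already planned. It should be settled before the economic analysis is run, because it defines the method for the primary endpoint.

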#### Cost‐utility analysis

2.7.4

The cost‐utility analysis will be performed with French and Spanish utility values estimated from EQ‐5D scores.

#### Primary clinical outcome analysis

2.7.5

Noninferiority will be considered to have been demonstrated if the upper value of the 97.5% one‐sided CI of the relative risk is inferior to the noninferiority margin equal to 1.25, in both the PP and ITT populations. If noninferiority of the restrictive strategy is established, sequential testing of superiority of the restrictive strategy will be accepted if the upper value of the 97.5% one‐sided CI of the relative risk is inferior to one.

All individual components of the primary outcome will be analyzed by Chi‐square or Fisher's exact tests. As these analyses will be exploratory, no adjustment of the alpha value for multiplicity will be made.

Times to death and MACE during 1‐year follow‐up will be described by Kaplan‐Meier curves and tested by log‐rank test. The reference date is defined as the randomization date. All patients will be censored at the time of the last observation.

All safety endpoints will be analyzed by Chi‐square or Fisher's exact tests.

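### Analysed alone, the nonfatal MI and nonfatal stroke components mix how often the event occurs with how often it kills, and can favour the arm with more lethal events

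*Protocol article*

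**What the plan says.** The composite in section 2.3 of the protocol article joins all-cause death with "nonfatal stroke, nonfatal recurrent myocardial infarction, or emergency revascularization prompted by ischemia". The footnote to Table 2 repeats this definition and adds that "All components of the composite outcome will also be analyzed separately".

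The stand-alone uses are:

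- **30 days, clinical.** Table 2 lists the components as exploratory outcomes. Section 2.7.5 says "All individual components of the primary outcome will be analyzed by" chi-square or Fisher's exact test, and continues: "As these analyses will be exploratory, no adjustment of the alpha value for multiplicity will be made".
- **1 year, clinical.** Table 2 says all components "of this composite clinical outcome will also be analyzed separately as secondary endpoints".
- **30 days, economic.** Table 2 says "ICERs for each individual component of the primary endpoint will be estimated separately". There is no matching row at 1 year.

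The sentence in section 2.7.5 does not contain the word nonfatal. The restriction comes from the Table 2 footnote, whose marker is attached to the word components in both the 30-day and the 1-year rows. Table 2 lists no endpoint for total MI or total stroke. The blinded events committee nevertheless reviews "All clinical outcomes (deaths, including cause of death, AMIs, strokes" and other events, with no limit to nonfatal ones.

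**The concern.** Inside a composite that already contains death, restricting MI and stroke to nonfatal events does no harm, because a fatal event is counted as a death. Once the component stands alone, that protection is gone. A patient who dies of a recurrent infarction falls on the same side of the two-by-two table as a patient who never had one. A treatment that turns nonfatal infarctions into fatal ones then appears to reduce infarction.

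Recurrent MI is a component that readers of this trial will look at closely. The Discussion cites a meta-analysis in cardiovascular patients with more acute coronary syndromes under restrictive strategies, and another with numerically more deaths in the AMI subgroup managed restrictively. If the trial concludes noninferiority, the MI line is one place where readers will look for a countervailing signal. The 30-day component ICERs use the same definition, so a strategy could be credited with averting infarctions that were in fact fatal.

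**Working it through.** **Inputs.** The document gives no figure for recurrent MI incidence or MI case fatality in either arm, so there is no planned value to reproduce. From section 2.7.1, 315 patients per arm are planned. All incidences and case fatalities below are assumptions.

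**Formula.** Let p be the risk of any recurrent MI, f the proportion of those MIs that are fatal, and R and L the restrictive and liberal arms. With all randomized patients in the denominator:

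- nonfatal MI risk = p × (1 − f)
- RR(nonfatal) = RR(any) × (1 − f_R) / (1 − f_L)

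**Equal incidence, different lethality.** Take p = 5% in both arms, so RR(any) = 1.00.

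| f_R vs f_L | Nonfatal MI, R vs L | Patients of 315 | RR(nonfatal) |
|---|---|---|---|
| 10% vs 10% | 4.5% vs 4.5% | 14.2 vs 14.2 | 1.00 |
| 30% vs 10% | 3.5% vs 4.5% | 11.0 vs 14.2 | 0.70/0.90 = 0.78 |
| 50% vs 10% | 2.5% vs 4.5% | 7.9 vs 14.2 | 0.50/0.90 = 0.56 |

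The incidence cancels, so these ratios are the same at 3% or 8%.

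**Unequal incidence.**

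- 6% vs 5% incidence, 40% vs 10% fatal: nonfatal 3.6% vs 4.5%. RR(any) = 1.20 but RR(nonfatal) = 0.80, so the direction reverses.
- 21 vs 15 infarctions, 40% vs 20% fatal: nonfatal 21 × 0.6 = 12.6 vs 15 × 0.8 = 12. RR(any) = 1.40 but RR(nonfatal) = 1.05.
- 26 vs 20 infarctions, 35% vs 20% fatal: nonfatal 26 × 0.65 = 16.9 vs 20 × 0.8 = 16. RR(any) = 1.30 but RR(nonfatal) = 1.06.

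**Effect on a component ICER.** In the 30% vs 10% row, the restrictive arm is credited with 4.5 − 3.5 = 1.0 nonfatal MI averted per 100 patients. No MI was averted, and fatal MI is 1.5% vs 0.5%, one more per 100.

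**Where the missing events go.** With 21 vs 15 infarctions, fatal MIs are 8.4 vs 3. That excess of 5.4 appears in the all-cause death component. Setting other events aside, MACE shows the full excess of 6 (5.4 fatal plus 0.6 nonfatal).

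**The case against.** The best defence is that nothing is lost overall. A fatal MI still counts in MACE and in all-cause death, and time to death over 1 year has its own Kaplan-Meier curves and log-rank test. Noninferiority, superiority and the primary ICER all rest on MACE. The 30-day component tests are declared exploratory. All of this stands and limits the weight of the point. It does not remove it: all-cause death also contains deaths from other causes and cannot show whether infarction became more frequent, and the exploratory label does not change what the estimate measures.

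Precision is also poor under either definition. For 21/315 vs 15/315, the standard error of log RR is √(1/21 − 1/315 + 1/15 − 1/315) = 0.329, which gives RR 1.40 with a 95% interval of about 0.74 to 2.67. Counting all MIs would not settle the matter; it would make the estimate address the right question.

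The text is also less firm than it looks. Nonfatal is not defined, so the handling of an MI followed days later by death is open and may be settled in documents not shown.

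Three stronger readings are tempting but unsupported:

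- **That the trial's main result is biased.** It is not, because MACE and the main ICER contain every death.
- **That the article gives reason to expect deadlier infarctions under restriction.** It cites more coronary events and numerically more deaths in some populations, says nothing about MI case fatality by strategy, and reports conflicting evidence, including two small ACS trials that point in opposite directions.
- **That 1-year component ICERs are affected.** None are planned.

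**Conclusion.** The point holds for the stand-alone MI and stroke analyses at 30 days and 1 year and for the 30-day component ICERs, and for nothing else. As defined, these components measure incidence × (1 − case fatality), and no total MI or total stroke endpoint offsets this. The algebra needs no assumption beyond the literal reading that a fatal event is not a nonfatal one. The size does: RR 0.78 instead of 1.00 requires case fatality of 30% vs 10% at equal incidence, and if case fatality is equal in the two arms the relative risk is not distorted at all. The change is worth making because it is cheap and these components will be used to interpret the composite. It does not threaten the primary conclusion.

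**What to change.** Leave nonfatal in the definition of MACE. For the stand-alone clinical analyses at 30 days and 1 year, and for the 30-day component ICERs, define the components as any recurrent MI (fatal or nonfatal) and any stroke (fatal or nonfatal), built from the committee's adjudicated events and "deaths, including cause of death". Report them next to all-cause death, and keep the nonfatal counts as the breakdown of the composite. State how an MI or stroke followed by later death is classified. Settle this before database lock.

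The change needs no additional patients, alpha or planned data collection. It has two modest costs. A fatal MI or stroke will appear under both death and its own component, so component results and component ICERs must not be added together; the report should say so. The total counts also depend on attributing deaths to a cause, which is less certain than all-cause death, for example when a sudden death is unwitnessed.

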### Subgroup analyses

2.8

Interactions between outcomes and prespecified subgroups will be analyzed according to the following variables: age, sex, body weight, diabetes mellitus, smoking status, hypertension, dyslipidemia, Killip class, type of AMI (ST‐segment elevation myocardial infarction [STEMI] or non‐STEMI), renal function at baseline, use of revascularization for acute coronary syndrome (ACS), hemoglobin at randomization, and presence or absence of overt bleeding before randomization.

